### Power calculation

The power of this observational cohort study and the number of participants is based on one of the clinical relevant primary endpoints: incidence of eczema after antibiotic exposure in early life. Eczema is the most common inflammatory skin disease of childhood, affecting 5 to 20 % of children at any time. The cumulative prevalence of eczema varies from 20 % in Northern Europe and the USA to 5 % in the south-eastern Mediterranean [43]. In high-risk populations in Northern Europe (e.g. infants with a positive family history of atopy), the incidence of eczema is increased and estimates 60 % [44]. Based on these data, in this study the incidence of eczema in the control group (healthy, non-antibiotic-treated infants) is estimated 20 %, whereas in the antibiotic-treated group (infants we assume at increased risk for developing eczema) the incidence may rise to 35 %. This percentage, to our opinion, reflects a slightly increased risk for developing eczema after antibiotic treatment in early life in a general population of infants. Assuming a dropout rate of 15 %, a total of 450 children (150 antibiotics, 300 controls) have to be included to demonstrate this difference (20 % ↔ 35 %) with a power of 80 % and an *alpha* of 5 %.

The prevalence of other disease outcomes is variable. For example, prevalence rates of infantile colic vary between 5 and 40 % [45], and literature shows that almost half of the children experience wheezing during the first years of life [46]. So far, the effect of antibiotics (prospectively investigated) on these frequencies is unknown. Defining the size of potential differences to capture is therefore limited.

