### Statistical analysis

We will evaluate the potential relationships between antibiotic use in early life and the various (clinical) endpoints. Variables are verified for normal distribution and *t*-tests will be used for testing the null hypothesis. Either logistic regression analysis or cox regression analysis will be applied to the data (appearance of the primary endpoint(s) will be recorded as specifically as possible), so that odds ratios or hazard ratios and their 95 % confidence interval can be presented for description of the relationships. Multivariate models will be used to assess confounders and confounding effects. We will perform post hoc analyses to look for potential effects of the different antibiotic regimes. Outcomes may, possibly, be classified into subgroups. According to antibiotic treatment after the first two weeks, children will be grouped based on the number of antibiotic courses during the first year of life (0 / 1 / 2 or more courses). Within the ‘treatment groups’ a distinction can be made between the class or spectrum of the prescribed antibiotics.

Microbiota composition will be described by means of abundance, diversity and (dis)similarity. Diversity is calculated using the Shannon index [42] and differences in this index will be tested with Mann–Whitney *U* test. Dissimilarities between samples, or between-sample diversity, are calculated as the cosine distance between each pair of samples and analyzed with principal coordinate analysis (PCoA). All statistical analysis will be conducted using SPSS version 22.0 (SPSS Inc., Chicago, IL, USA) and the vegan software package in R (Foundation for Statistical Computing, Vienna, Austria).

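### The stated inputs do not give 450 infants: they require about 357 to 393 for 80% power, and 150/300 with 15% dropout has about 85–88% power (a conservative, minor error)

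*Protocol article*

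**What the plan says.** The section Power calculation sizes the study on eczema, "based on one of the clinical relevant primary endpoints: incidence of eczema after antibiotic exposure in early life". It fixes these inputs:

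- Control group: "the incidence of eczema in the control group (healthy, non-antibiotic-treated infants) is estimated 20" percent.
- Antibiotic group: "the incidence may rise to 35" percent.
- Attrition: "Assuming a dropout rate of 15" percent.
- Target: "with a power of 80" percent, at an alpha of 5%.

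From these it concludes that "a total of 450 children (150 antibiotics, 300 controls) have to be included to demonstrate this difference". The Abstract, Background, Study design and population, and Discussion repeat 450 or 150/300 but give no other basis for the number. The section Statistical analysis adds that "Multivariate models will be used to assess confounders and confounding effects". The power calculation makes no reference to that adjustment.

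**The concern.** The section gives both rates, the allocation, the dropout, the power and the alpha, so the total can be checked directly. It presents 450 as the number these inputs require, yet the usual formulas give a clearly smaller number. Required size and power therefore do not belong together.

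What is at stake is how the design is described. A reader of a null eczema result would take the chance of missing a 15-point difference to be 20%, when the stated inputs put it at about 12–15%. That reader would also take 35% as the rate detectable with 80% power, when it is about 33–34%. If part of the 450 was a deliberate margin, the text does not show it.

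**Working it through.** **Inputs** (all from Power calculation): p1 = 0.35 (antibiotics), p2 = 0.20 (controls), 150 and 300 infants (1:2, so k = 2), dropout 15%, power 80%, alpha 5%. Sidedness is not stated. I assume two-sided, so z(0.975) = 1.960 and z(0.80) = 0.842.

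**Step 1. Try to reproduce 450, pooled formula.**

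n1 = [1.960·√(p̄(1−p̄)(1+1/k)) + 0.842·√(p1(1−p1) + p2(1−p2)/k)]² / (p1−p2)²

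- p̄ = (0.35 + 2×0.20)/3 = 0.25
- First root: √(0.1875×1.5) = √0.28125 = 0.5303
- Second root: √(0.2275 + 0.0800) = √0.3075 = 0.5545
- n1 = (1.0394 + 0.4667)²/0.0225 = 2.268/0.0225 = 100.8, so 101 treated and 202 controls
- After dropout: 101/0.85 = 118.8, so 119 + 238 = **357**

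**Step 2. With continuity correction.**

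n1' = (n1/4)·[1 + √(1 + 2(k+1)/(n1·k·(p1−p2)))]²

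- With n1 = 100.8: (100.8/4)·[1 + √(1 + 6/30.25)]² = 110.6, so 111 + 222
- After dropout: 111/0.85 = 130.6, so 131 + 262 = **393**

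**Step 3. Other routes to 450 at 80% power.**

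| Variant | Total after 15% dropout |
|---|---|
| Pooled, dropout added as n×1.15 | 351 |
| Arcsine | about 362 |
| Fisher exact | roughly 375–381 |
| Unpooled variance | about 379 |
| Continuity-corrected, n×1.15 | 384 |
| 1:1 allocation, pooled / corrected | 325–326 / 356 |
| One-sided, pooled / corrected | 285 / 318 |

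None reaches 450. The nearest match found is the continuity-corrected formula at 85% power (447), but the article states 80%. The gap from 450 is 450 − 393 = 57 to 450 − 357 = 93 infants, that is 13% to 21% of the stated total, which is too much for rounding.

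**Step 4. Power of the stated design.** 150×0.85 = 127.5 and 300×0.85 = 255; I use 127 and 255.

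- SE under the null: √(0.2499×0.7501×(1/127 + 1/255)) = 0.0470
- SE under the alternative: √(0.2275/127 + 0.16/255) = 0.0492
- Pooled: Φ((0.15 − 1.960×0.0470)/0.0492) = Φ(1.176) = **88.0%**
- Continuity correction, c = ½(1/127 + 1/255) = 0.0059: Φ((0.15 − 0.0059 − 1.960×0.0470)/0.0492) = Φ(1.056) = **85.5%**
- Unpooled variance: 86.2%; Fisher exact: 87.1%
- No dropout at all (150/300), pooled: 92.5%

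**Step 5. Detectable rate with 80% power at 127/255, controls at 20%.** Solving the Step 4 expressions for p1 gives 33.2% (pooled) and 33.9% (continuity-corrected).

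**The case against.** The strongest reply is that the error does no harm. Under every two-sided variant the planned 450 infants exceed 80% power, so the study can do what the section promises. A reader who relies on the stated 80% is only slightly too cautious, and a null result would in any case be read mainly from the odds or hazard ratio and its 95% confidence interval, which the section Statistical analysis says will be presented. All of this stands, and it makes the point minor.

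A second reply is that 450 may contain a sensible margin. Eczema is only one of the primary endpoints, and confounder adjustment is planned. At alpha 0.025, for example, the pooled power at 450 is 81.9%. This shows that 450 is a reasonable size. It does not rescue the sentence, which derives 450 from the 20% versus 35% contrast, 15% dropout and alpha 5% alone.

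A third reply is that an article condenses the full protocol. That excuses the unstated test, sidedness and formula, and I do not count these as faults. It does not cover a set of inputs paired with a result they do not yield.

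Two stronger readings are tempting, and the documents do not support them:

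- A reader might infer that the stated power would be right only if dropout were near 33%. That holds for the pooled formula (1 − 101/150 = 0.33). With continuity correction it is about 26% (1 − 111/150).
- A reader might try to put a figure on the power left after confounder adjustment. That needs the share of exposure variance that the confounders explain, and the documents give no such value.

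**Conclusion.** The point holds as a minor, conservative error. On the stated inputs, 80% power needs about 357 infants (pooled) to 393 (continuity-corrected), and 150/300 with 15% dropout has about 85–88% power. This assumes a two-sided 5% test at 1:2 allocation and dropout applied by dividing by 0.85. A one-sided test would widen the discrepancy.

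A reader might infer that the study is badly sized, either underpowered or in need of a smaller sample. Neither follows. Power for the crude eczema contrast is above target, and a margin may well be useful given the planned adjustment and the several endpoints. The fault is that the article presents 450 as the number its inputs require, in its only sample-size justification.

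**What to change.** Keep 150/300. Delete the statement that 450 infants are needed for 80% power and replace it with, for example:

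> With 15% dropout (127/255 evaluable) the study has about 88% power (85% with continuity correction) for 20% versus 35% at two-sided 5%, or 80% power for 20% versus about 33% (34% with continuity correction).

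If the extra size was intended as an allowance for confounder adjustment or for several primary endpoints, state that allowance and its size instead, so that 450 can be derived from what is written. The cost is a sentence or two; recruitment and analysis do not change.

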## Discussion

To the best of our knowledge, this is the first prospective observational cohort study, with a follow-up of one year, addressing clinical outcomes after empiric antibiotic treatment in early life which at the same time investigates the development of intestinal microbiota composition after this antibiotic exposure. Subsequently, extensive clinical outcomes can be linked to microbiota composition over time. This study includes a total of 450 infants, of whom 150 are exposed to antibiotic treatment shortly after birth and 300 controls. Previous studies addressing consequences of antibiotic treatment in early life were hampered by a retrospective approach [11, 33, 39, 47], divergent study populations [48], smaller sample sizes [17] or a limited period of follow-up [34, 49].

By assessing an extended number of clinical parameters in a fairly large group, and subsequently strictly selected homogeneous subgroups of infants, bias due to confounding factors such as mode of delivery and type of feeding is expected to be reduced. Results from this study may improve our understanding of the evolving microbiota in term infants. Also, by collecting fecal samples at eight time points during the first year of life and around the second birthday, long-term microbiota development can be investigated.

The fact that children who are sick and receive antibiotic treatment may differ from healthy children, who do not need antibiotic treatment at birth, is one of the most important limitations of this study. However, to our opinion, there are no opportunities to bypass this problem, as ethical concerns prevent us from performing a double blind randomized controlled trial. Another limitation of this study may be the fact that bacterial composition may change as a consequence of freezing fecal samples. For example, levels of *Bacteroidetes* have been shown to be reduced in frozen samples [3, 50, 51]. As all samples will be obtained by the parents and stored in their home freezers, no information on potential differences in storage conditions between samples can be obtained. We try to minimize this variation by instructing (by one of the investigators) all parents on how to collect the faecal samples, which makes the collection procedure as standardized as possible. We do realize that studying the microbiota composition of fecal samples may not be the best method to assess the general composition and the effect of antibiotics in the gastrointestinal tract. Stool samples therefore are used as a proxy for the study of the gut microbiota as these samples are easier to collect than biopsy samples and avoid invasive procedures (and associated ethical issues). A limitation of sampling the gut microbiota is that once the sample is taken, alterations in the relative proportions of various bacterial species can occur so that the sample might no longer accurately reflect the composition of the microbiota in vivo by the time it is processed [3]. This is a well-known problem with respect to molecular approach of microbiota composition and to date it is impossible to collect biopsy samples from infants (and healthy volunteers generally) on a large scale due to the practical and ethical challenges indicated above [3].

IS-pro will be used to characterize the microbiota, because this technique has specifically been designed for application in a clinical setting. It has been validated for clinical diagnostics, which makes it fully reproducible and the high-throughput nature of IS-pro makes analysis of a large number of samples feasible. IS-pro comprises two separate phylum-specific PCR reactions though, which hampers direct comparisons of relative abundances addressing all three phyla together [41]. Next to that, IS-pro does not generate sequence data in the conventional sense. This means IS-pro cannot achieve the same level of detail as next-generation/whole genome sequencing techniques (e.g. Illumina), although sequence data confirmed specificity of IS-pro in (currently) numerous peaks, underlining the validity of the technique [41].

There is now sufficient evidence to conclude that antibiotic treatment in early life has a detrimental effect on the gastrointestinal microbiota composition. However, it is still unclear as to what extent the composition is disturbed and for how long the gastrointestinal dysbiosis remains, if and how microbiota composition will ‘normalize’ and what the effects are on the developing immune system. These findings can be important, since there is evidence that the manipulation of infant microbiota by using pre-or probiotics can restore the ecological balance of the microbiota [34, 52, 53]. If our hypothesis is proven with this study, future studies should demonstrate if targeted intervention, by using dietary supplements, pre- or probiotics or otherwise, may have beneficial effects by limiting the gastrointestinal imbalance due to early antibiotic exposure.

## Abbreviations

GITI: gastrointestinal tract infections
ICPC: International Classification system of Primary Care
LRTI: lower respiratory tract infections
OTU: operational taxonomic unit
PCoA: principal coordinate analysis
PCR: polymerase chain reaction
RTI: respiratory tract infections
SD: standard deviation
URTI: upper respiratory tract infections
